## Abstract

**Background:**

Arthritis gloves are regularly provided as part of the management of people with rheumatoid arthritis (RA) and undifferentiated (early) inflammatory arthritis (IA). Usually made of nylon and elastane (i.e. Lycra**®**), these arthritis gloves apply pressure with the aims of relieving hand pain, stiffness and improving hand function. However, a systematic review identified little evidence supporting their use. We therefore designed a trial to compare the effectiveness of the commonest type of arthritis glove provided in the United Kingdom (Isotoner gloves) (intervention) with placebo (control) gloves (i.e. larger arthritis gloves providing similar warmth to the intervention gloves but minimal pressure only) in people with these conditions.

**Methods:**

Participants aged 18 years and over with RA or IA and persistent hand pain will be recruited from National Health Service Trusts in the United Kingdom. Following consent, participants will complete a questionnaire booklet, then be randomly allocated to receive intervention or placebo arthritis gloves. Within three weeks, they will be fitted with the allocated gloves by clinical specialist rheumatology occupational therapists. Twelve weeks (i.e. the primary endpoint) after completing the baseline questionnaire, participants will complete a second questionnaire, including the same measures plus additional questions to explore adherence, benefits and problems with glove-wear. A sub-sample of participants from each group will be interviewed at the end of their participation to explore their views of the gloves received. The clinical effectiveness and cost-effectiveness of the intervention, compared to placebo gloves, will be evaluated over 12 weeks. The primary outcome measure is hand pain during activity. Qualitative interviews will be thematically analysed.

**Discussion:**

This study will evaluate the commonest type of arthritis glove (Isotoner) provided in the NHS (i.e. the intervention) compared to a placebo glove. The results will help occupational therapists, occupational therapy services and people with arthritis make informed choices as to the value of arthritis gloves. If effective, arthritis gloves should become more widely available in the NHS to help people with RA and IA manage hand symptoms and improve performance of daily activities, work and leisure. If not, services can determine whether to cease supplying these to reduce service costs.

**Trial registration:**

ISRCTN Registry: ISRCTN25892131 Registered 05/09/2016

**Electronic supplementary material:**

The online version of this article (doi:10.1186/s12891-017-1583-4) contains supplementary material, which is available to authorized users.

## Background

Rheumatoid arthritis (RA) is a chronic inflammatory condition causing joint pain, swelling (synovitis), stiffness and muscle loss around affected joints [1]. It affects 1% of the population, and twice as many women as men. Peak onset is in the 40-60 age group, it is incurable and causes significant disability if untreated [2, 3]. RA is managed with disease modifying anti-rheumatic drugs (DMARDs), rehabilitation and self-management education. People with persistent synovitis, where other pathologies are ruled out (i.e. undifferentiated inflammatory arthritis (IA), who do not yet meet the criteria for RA [4]), also require specialist care and DMARDs, and are thus treated as if they have RA [1]. Most people with IA and RA have symptoms in both hands, resulting in problems with everyday activities, work and leisure. Many experience frustration and distress because of hand pain, stiffness and disability. A third are work disabled within 5 years [1].

Arthritis gloves are commonly provided by Rheumatology occupational therapists to people with IA or RA. These are worn for pain relief during the day or night and to improve hand function during the day. We surveyed Rheumatology occupational therapists,﻿﻿identifying that most provide arthritis gloves [5]. Provision varies considerably between occupational therapists but averages a third of the patients they see. The most common make of glove provided is the mid-finger Isotoner glove (i.e. finger tips exposed to aid hand function) and the next commonest are Jobskin and Norco oedema gloves [5, 6]. Provision of gloves appears to have risen following a randomised controlled trial (RCT) demonstrating an alternative treatment (resting splints) was ineffective in early RA [7]. (Glove photographs are in Additional file 1: study information).

Arthritis gloves are usually made of nylon and elastane (i.e. Lycra®). They are thought to impact on hand symptoms through providing compression (pressure) and/or warmth. Some models apply both and others warmth only. Isotoner gloves, containing 20% elastane, exert the highest pressure of those makes available, at 23-32 mmHg [8]. Other makes exert less as these contain less elastane (e.g. the Jobskin classic oedema gloves exert 15-25 mm Hg and contain 11% elastane [9]). When properly fitted (to be a “snug fit”), the gloves apply controlled pressure to the hand [10]. The pressure is thought to: (a) remove extracellular fluid, thus reducing pain, stiffness and improving finger motion; and (b) increase blood flow and consequently warmth, reducing pain [10, 11]. The glove material also provides warmth, contributing to pain relief. Makes of arthritis gloves, which specifically apply pressure, are termed compression or oedema gloves. It is unclear what a therapeutic level of pressure is, as this has not been identified through physiological studies. However, based on pressure information from manufacturers, therapists consider this is between 15-32 mmHg. We also hypothesize that arthritis gloves provide tactile feedback to the glove wearer reminding them to take more care of their hand joints. Potentially, all models of glove (however much pressure and/or warmth they apply) may be acting through this mechanism. This effect was hypothesized in a pilot clinical effectiveness and efficacy trial of thumb splints [12].

Despite their widespread use, evidence for the effectiveness of arthritis gloves is inconclusive. In a recent systematic review, we identified only four trials evaluating arthritis gloves. Trials were small and results inconclusive [13]. We therefore developed this randomized controlled trial to evaluate the effectiveness and cost-effectiveness of the most commonly used arthritis glove (i.e. Isotoner) in people with RA or IA.

### Feasibility study

We conducted a feasibility study among patients with IA or RA (*n* = 39) in 10 Occupational Therapy departments in Northwest England evaluating mid-finger Isotoner gloves (as these are the commonest type provided and apply the highest pressure). During this study we standardised arthritis glove eligibility criteria, glove treatment protocols (including the arthritis glove patient information sheet) with participating therapists (North-West College of Occupational Therapy Specialist Section in Rheumatology: NWCOTSS-R arthritis glove protocol [14]. The results of the study are reported elsewhere [15].

#### Objectives

The primary objective is to assess whether there is a clinically important difference in self-reported dominant hand pain during daytime activity between participants with RA or IA receiving intervention gloves (Isotoner gloves) in addition to usual care compared to participants receiving placebo gloves (Jobskin classic oedema gloves fitted at least one size too big to ensure similar warmth is provided but minimal pressure only is applied), plus usual care.

The secondary objectives are to:i.assess the effectiveness of intervention gloves, relative to placebo gloves on self-reported: non-dominant hand pain during activity; dominant and non-dominant nocturnal hand pain; hand pain during the day at rest; hand stiffness; hand joint swelling; and hand function.ii.evaluate the cost-effectiveness of arthritis gloves compared with placebo gloves, taking into account the cost of the gloves and other healthcare resources used by participants.iii.explore participants’ views of: the effects of arthritis (intervention) and placebo gloves on hand symptoms, function, and their daily lives; acceptability of glove wear; and how and when they prefer to use these.

#### Trial design

The A-GLOVES trial is a pragmatic, patient-blinded, multi-centre, superiority randomised parallel group trial of intervention gloves compared to placebo gloves in people with RA or IA and persistent hand pain affecting their ability to do daily activities. Analysis will be on an intention-to-treat basis. Ethical approval for this study has been obtained from the North of Scotland Local Research Ethics Committee [15-NS-0077]. The study protocol was developed using the SPIRIT guidelines [16].

## Methods

### Study setting

Study participants will be recruited from Rheumatology, Occupational Therapy and Hand Therapy departments in 23 hospitals across 17 NHS Trusts in England and Scotland in the United Kingdom (UK), as arthritis gloves are most commonly provided by rheumatology occupational therapists in secondary care.

### Eligibility criteria

#### Inclusion criteria

Patients eligible for the trial must comply with all of the following at randomization:Aged ≥18 yearsDiagnosed with RA or IA by a Rheumatology ConsultantHave persistent pain in the proximal interphalangeal (PIPs) and/or metacarpophalangeal (MCP) joints causing eitheri)difficulty using their hands during the day (for day wear of gloves) orii)disturbed sleep (for night wear of gloves) oriii)limited ability to use their hands when waking/in the morning (for night wear of gloves)4.Willing to wear arthritis gloves and participate in the trial5.Able to read and understand English and,6.Can provide informed consent.

#### Exclusion criteria

People will be excluded from the study who have:Been diagnosed with other rheumatic conditions, such as gout, psoriatic arthritis, ankylosing spondylitis, connective tissue disorders (systemic lupus, systemic sclerosis), resulting in inflammatory arthritis in the hand/sSevere Raynaud’s disease or other circulatory disturbances in the handSevere neuropathies (nerve damage) in the handSevere hand deformitiesAny contraindications to wearing the gloves (e.g. eczema, infections, broken skin)Previously worn arthritis gloves.

### Interventions

#### Occupational therapist training in glove provision

Interventions will be delivered by 27 National Health Service (NHS) Rheumatology occupational therapists (≥Band 6 i.e. clinical specialists). Participating therapists must attend a one-day clinical trial training programme delivered by expert Rheumatology occupational therapists and the research team. This will include: trial background; key study procedures; and practice in providing the intervention and placebo gloves in a standardised manner. The A-GLOVES Occupational Therapy Glove Provision Manual, developed by the research team with the NW-COTSS-R, will be followed when fitting these gloves [17].

In addition to the training day, the Trial manager will conduct site visits to ensure all Principal Investigators, research facilitator/s (i.e. nurses/other staff employed in the NHS to assist with recruitment into trials) and occupational therapists involved in the study understand how to explain the study and arthritis gloves appropriately, to ensure participants are not unblinded to the intervention.

#### Glove fitting

The intervention group will receive correctly fitted mid-finger length Isotoner arthritis gloves. The placebo group will receive mid-finger length Jobskin classic oedema gloves fitted at least one size too large, to ensure they do not apply therapeutic levels of compression. When fitting gloves, the occupational therapist will measure participants’ MCP circumference to determine the glove size required. Therapists will also use their clinical judgement to determine appropriate fit. Usually, patients requiring gloves receive these for both hands as their hand pain and/or swelling is bilateral. However, if patients have unilateral pain and/or swelling, they are provided with a glove only for the affected hand.

#### Additional Interventions

All participants (in both intervention and placebo groups) will receive a booklet about hand self-management: “Looking After Your Joints when you have arthritis” [18]. This booklet is widely provided in clinical practice. They will also receive an information sheet about hand exercises, based on the Strengthening And Stretching For Rheumatoid Arthritis of the Hand (SARAH) trial hand exercise programme for RA [19, 20]. During the 12 weeks, participants will only receive brief training in joint protection and hand exercises, and this will not use cognitive-behavioural approaches. Most departments do not normally offer behaviourally based joint protection and/or hand exercise programmes (or where these exist, such programmes usually have waiting lists), thus participants are not being disadvantaged.

#### Modifications

In some instances, a glove may not be fitted if enlarged PIP joints or finger deformity prevent this. For those participants with an MCP circumference greater than 23.5 cm (or fingers/hands too large in other respects), no gloves will be fitted, as an appropriately large size is not available from manufacturers. If the participant cannot be fitted with gloves, they still remain in the trial, in line with “intention-to-treat.”

#### Adherence

Recommendations for when to wear gloves will be based on individual needs; most, but not all, patients will be provided with gloves for both hands. Most people experience hand pain during the day and are recommended to wear gloves during activity. Those experiencing hand pain at night, which interferes with sleep, will also be recommended to wear gloves at night. Gloves are not recommended to be worn continually. All participants will receive written information about glove wear and care, using the sample information sheet in the A-Gloves Occupational Therapy Glove Provision Manual [17].

To check for correct glove fit and any problems, occupational therapists will either: within two to four weeks of glove provision offer a review appointment (in person or by telephone); or ask the participant to get in contact if experiencing problems, if this is their normal departmental policy. At the review appointment, participants will be reminded about their glove wear regimen and the need to continue to wear the gloves until the 12-week follow-up questionnaire is completed. At the end of their trial participation, they will be contacted with further instructions about future glove wear.

Adherence to glove wear will be assessed in the 12-week follow-up questionnaires, by asking participants to describe their glove wear for right and left hand gloves. This will include, over the last four weeks, the: average time worn during the day and/or at night; and the average number of days per week gloves were worn. The participant will also be asked to state whether they have obtained arthritis gloves from elsewhere (if they did so, as it is possible for patients to purchase gloves in shops and on-line) and glove wear related to these (if applicable).

#### Concomitant care

Occupational therapists are asked not to provide resting, wrist, finger or thumb splints or any other occupational therapy interventions (apart from joint protection and hand exercises) to participants whilst they are in the trial (i.e. during their 12 weeks participation). However, participants are permitted to attend Physiotherapy for lower limb interventions if required. Data on participants’ use of concomitant care is collected via the 12-week questionnaire.

### Outcomes

The primary outcome measure is ‘hand pain during moderate activity’ which was considered the most important outcome by glove-users in our feasibility study. This is measured as hand pain in the dominant hand during the day, on a typical day, when doing moderate hand activities, e.g. housework, cooking, Do-It-Yourself, gardening. In our feasibility study, 2% of participants received one glove for their non-dominant hand only. It is therefore possible that the primary outcome cannot be collected in a small number of participants in this trial.

Secondary outcome measures are hand pain when resting and at night; stiffness; self-reported hand condition; hand function; disability; and resource use and costs to measure cost-effectiveness of glove provision (Table 1).

**Table 1 Tab1:** Content of the Baseline and 12-week follow-up questionnaires

Concept	Measurement method	Details	0-wks	12-wks
*Demographic and Condition Information*	Date of birth		✓	
	Gender		✓	
	Time since RA or IA symptom onset		✓	
	Time since RA or IA diagnosis		✓	
	Employment status		✓	
	Marital status		✓	
	Living status (alone; or with family/significant others)		✓	
	Medication regimen (i.e. what drugs do they take for their arthritis);		✓	
	Whether received a steroid injection/oral steroid in the last 6 weeks		✓	
	Hand dominance (i.e. whether they consider this to be right, left or both).		✓	
*Primary outcome*	Hand Pain during activity	0-10 (0 = no pain/10 = severe pain) point numeric rating scale of hand pain in the dominant hand during the day [21]	✓	✓
*Secondary outcomes*	Hand Pain	0-10 (0 = no pain/10 = severe pain) a) during a typical day during activities in the last week in the non-dominant hand; b) when resting- separately for the dominant and non-dominant hands; and c) at night –separately for the dominant and non-dominant hands.	✓	✓
	Stiffness	Measured separately for the dominant and non-dominant hands: a) Patient self-reported duration of early morning stiffness affecting the hands (hours/min) b) 0-10 point numeric rating scale of hand stiffness (no (0) and severe (10) hand stiffness)	✓	✓
	Self-reported hand condition	a five point rating scale of very severe/severe/moderate/good/very good.	✓	✓
Hand Function	The Measure of Activity Performance of the Hand (MAPHAND) [22, 23]	a self-reported measure of 18 items of performing daily activities with the hands	✓	✓
	The Michigan Hand Outcomes Questionnaire (MHQ) [24, 25]	assesses right and left hands separately: physical status of the hand (movement, strength, sensation: 5 items); daily activities performed with the hands/arms (5 right and left; 7 bilateral); impact of their condition on their normal activities (5 items); pain frequency, severity and impact (5 items); perceived appearance of their hands (4 items); satisfaction with hand abilities (6 items)	✓	✓
Disability	The Health Assessment Questionnaire [26]	24 items of daily function	✓	✓
Economic analysis	EQ5D-3 L [27, 28]	5-items Scale (Mobility; Self-care; Usual activities; Pain/Discomfort; Anxiety/Depression	✓	✓
	Your use of NHS and social services	a) Any planned hospital overnight stays in the last 3 months b) List of planned admissions	✓	✓
	Your use of hospital out-patient appointments	a) Any planned hospital outpatient appointments lasting 4 h or less in the last 3 months b) If yes, department, speciality and number of appointments	✓	✓
	Your use of day hospital appointments	a) Any day or hospital outpatient lasting more than 4 h but not overnight during the last 3 months b) If yes, department, speciality and number of appointments	✓	✓
	Your use of accident and emergency services	a) Any A&E attendance in the last 3 months b) If yes, the number of visits did not lead to hospital admission c) Were admitted into a hospital as an in-patient from the A&E d) If yes, department, reason for admission, where and when admitted	✓	✓
	Your use of primary and community based health services	a) Use of services such as GP, Practice nurse, Nurse, Counsellor in the last 3 months b) If yes, number of visits to each	✓	✓
	Your use of primary and community based health services	a) Use of services such as, occupational therapy, Physio, Care worker, Home help, Social worker, Other in the last 3 months b) If yes, number of visits to each	✓	✓
Medication	Current medication for RA/IA			✓
	Any steroid injection/oral steroids started in the last 12 weeks	Yes/No		✓
	If yes, the date of the injection/started taking oral steroids	DD/MM/YY		✓
Health Status	Your own health state today	Measured by a 0-100 vertical scale (0 = worst imaginable state & 100 = best imaginable health state)		✓
Additional outcomes	Any other upper limb occupational therapy or physiotherapy treatment received in the last 12 weeks	Type of treatment received		✓
	Whether purchased or obtained from elsewhere, any other “arthritis” gloves.	Yes/No		✓
	If yes, what type these were			✓
	How their hands are in comparison to 12 weeks ago, i.e. before receiving gloves	(much better/better/no change/worse/much worse)		✓
	Concurrent use of any resting, wrist, finger or thumb splints			✓
	Adherence to glove wear	During the day and at night for right/left hand gloves; average time worn at night/during the day; average number of days per week gloves have been worn		✓
	Whether participants considered gloves provided any benefit	Yes/No		✓
	Whether they will continue to wear the gloves provided	Yes/No		✓
	If they considered the gloves of any benefit, what were these			✓
	Any problems encountered when wearing gloves	Freetext		✓

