### Sample size

This was calculated using data from the feasibility study. Minimal clinically important differences for pain scales in RA are estimated as 1.1 points on a 0–10 scale [31, 32]. The mean change in hand pain score during activity (measured four weeks post-intervention) was -1.03 (SD 2.22). As the SD from the feasibility data might be an underestimate, the 80% upper one-sided confidence limit of the estimated SD, i.e. 2.48 was used. To identify a 1.1 point difference, SD = 2.48, p = 0.05 and 80% power, 80 participants are required per group. Allowing for a 20% attrition (i.e. non-return of 12 week questionnaire and a small number (up to 2%) not receiving a glove for their dominant hand (because they only require a glove for their non-dominant hand, and therefore not providing primary outcome data), we intend to recruit 205 participants.

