### Statistical methods

Primary effectiveness analyses will follow a pre-specified statistical analysis plan and will include the intention to treat (ITT) population. The primary analysis will use multiple linear regression to estimate the effect of group allocation on hand pain during activity, controlling for the stratification variable in the randomisation process (recent DMARD changes) and for the baseline value of the hand pain score. Secondary analysis will repeat the primary analysis method for all other outcomes, using appropriate modelling approaches (i.e. multiple linear regression, logistic regression or ordinal logistic regression, controlling for the stratification variable and the baseline value of the specific measure. Sensitivity analyses will assess for any potential bias in the analysis of the primary outcome measure by excluding participants who were not given gloves, were given the wrong gloves, or who received steroids (oral or injection) between randomisation and outcome measurement (per protocol populations). Data will be analysed by person and using dominant hand results, as reported by the participant. No interim outcome analysis or sub group analysis will be undertaken. We will not undertake any data imputation for the primary analysis. We will undertake multiple imputation of the primary outcome as a sensitivity analysis. Questionnaire responses on medication use, other treatments, perceived benefit of gloves, continued glove use, adherence and occupational therapist treatment record data will be reported as numbers/proportions or means/SD, with 95% confidence intervals. Analyses will be undertaken in Stata version 14 or later [33].

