#### Economic evaluation

The economic analysis will include costs to health and social care service providers and health benefits to patients. The time horizon for the evaluation is 12 weeks as per the scheduled trial follow-up. As such neither costs nor outcomes will be discounted. The data will be analysed on an intent-to-treat basis.

The measure of health benefit for the primary economic analysis will be quality adjusted life years (QALYs). This will be estimated from the EQ-5D-3 L and associated utility tariffs. Secondary analysis will explore the cost-effectiveness of arthritis gloves using the primary clinical outcome measure, change in hand pain during moderate activity between baseline and follow-up. The direct costs of healthcare resources used during the trial will be estimated by combining the level of use reported by participants with the unit cost specific to that resource. The unit costs will be derived from published national average unit cost data, the price year will be 2016. Total direct costs will also include the cost of the gloves. Regression analysis will be used to estimate the net total costs and economic benefits of the arthritis gloves compared to the placebo gloves, adjusting for baseline values and the stratification variable (recent DMARD changes).

Cost-effectiveness will be measured as an incremental cost-effectiveness ratio (ICER) for the arthritis gloves versus the placebo gloves. As recommended by NICE for health technology appraisals [34], cost-effectiveness acceptability analysis will be conducted. Non-parametric bootstrapping of the incremental costs and outcomes (estimated from the regression analysis) will be used to estimate the probability that arthritis gloves are cost-effective compared to placebo gloves.

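### The 0-100 health-state scale is scheduled at 12 weeks only, so it lacks the baseline value that the general rule for secondary analyses would use (minor)

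*Protocol article*

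**What the plan says.** Table 1 in Outcomes is titled "Content of the Baseline and 12-week follow-up questionnaires" and has one column for each time point. Its Health Status row asks for the participant's own health today: "Measured by a 0-100 vertical scale (0 = worst imaginable state & 100 = best imaginable health state"). The 0-week cell is empty and the 12-week cell is ticked. The rows for hand pain, stiffness, hand condition, MAPHAND, MHQ, HAQ and EQ-5D-3L carry both ticks.

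Statistical methods sets one general rule: "Secondary analysis will repeat the primary analysis method for all other outcomes", using linear, logistic or ordinal logistic regression as appropriate, "controlling for the stratification variable and the baseline value of the specific measure". It then lists items to be summarised as proportions or means (medication, other treatments, perceived benefit, continued use, adherence, treatment records). Health status is not in that list.

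Outcomes names the secondary measures in its text: "Secondary outcome measures are hand pain when resting and at night; stiffness; self-reported hand condition; hand function; disability; and resource use and costs". The 0-100 scale is not among them. Economic evaluation bases QALYs on another instrument: "This will be estimated from the EQ-5D-3 L and associated utility tariffs".

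**The concern.** A rating of health today can be asked before gloves are fitted just as well as after. Most of the other items asked only at 12 weeks could not be: adherence, benefit from the gloves, problems with wear, and the comparison with 12 weeks earlier have no meaning at baseline. Current medication and steroid use do have baseline counterparts in Table 1. The health-state scale has none. The Abstract describes the second booklet as repeating the first and adding questions on adherence, benefits and problems with glove wear; a general health rating is none of those additions, so on that description it belongs with the repeated measures.

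The baseline value is usually the strongest available predictor of the same measure at follow-up, and it cannot be recovered once a participant has been randomised and fitted. A statistical analysis plan can choose a model, but it cannot supply a measurement that the schedule omits. At stake is some precision in comparing the arms on this one scale.

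**Working it through.** **1. The plan's own figure.** The only sample-size calculation concerns hand pain: "To identify a 1.1 point difference, SD = 2.48, p = 0.05 and 80% power, 80 participants are required per group". The SD is deliberately cautious ("the 80% upper one-sided confidence limit of the estimated SD, i.e. 2.48 was used"). With two-sided 5% (sidedness is not stated, but this reproduces the figure) and 80% power:

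n per group = 2 × (1.960 + 0.842)² × (2.48 / 1.1)² = 2 × 7.85 × 5.08 ≈ 79.8, so 80. Power at 80 per group is 0.801.

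Total recruited: 160 / (0.80 × 0.98) = 204.1, rounded up to 205.

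The stated figures reproduce. They rest on hand pain alone, which is collected at both times, so this point does not touch them.

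**2. Schedule against analysis rule.**

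| Measure | 0 weeks | 12 weeks | Named as secondary or economic outcome in the text |
|---|---|---|---|
| Pain, stiffness, hand condition, hand function, HAQ | yes | yes | yes |
| EQ-5D-3L | yes | yes | yes (QALYs) |
| 0-100 health state | no | yes | no |
| Hands compared with 12 weeks ago | no (none possible) | yes | no |

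The empty 0-week cell follows the same pattern as the neighbouring rows asked only at 12 weeks. Own-baseline adjustment can be carried out for every named patient-reported outcome. It cannot be carried out for the 0-100 scale.

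**3. Cost in precision.** Let r be the correlation between baseline and 12-week values of the scale. The document gives no r and no SD for it, so r is an assumption. Adjusting for the scale's own baseline multiplies the variance of the arm difference by (1 − r²). Leaving it out therefore multiplies the standard error by 1/√(1 − r²). With 80 analysed per arm, the difference detectable at 80% power is (1.960 + 0.842) × √(2/80) = 0.443 SD without the baseline, and 0.443 × √(1 − r²) with it.

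| Assumed r | 1 − r² | Standard error factor without baseline | Detectable difference with baseline (SD) | Participants per arm giving, with baseline, the precision of 80 without |
|---|---|---|---|---|
| 0.4 | 0.84 | 1.09 | 0.406 | 67.2 |
| 0.5 | 0.75 | 1.15 | 0.384 | 60.0 |
| 0.6 | 0.64 | 1.25 | 0.354 | 51.2 |
| 0.7 | 0.51 | 1.40 | 0.316 | 40.8 |

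Over a wider range, r = 0.3 gives 1.05 and r = 0.8 gives 1.67. The figure of 80 per arm is borrowed from the primary outcome. Numbers for this scale could be lower, because the telephone minimal data set in Data collection methods does not list it. The standard error factor does not depend on n.

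**4. Why these factors are upper bounds.** They compare own-baseline adjustment with no useful baseline covariate at all. The stratification variable and the baseline EQ-5D-3L and HAQ are available and may recover part of the loss. If such a proxy correlates q with the 12-week scale, the factor becomes √((1 − q²)/(1 − r²)). As an illustration, assumed q = 0.3 and r = 0.5 give √(0.91/0.75) = 1.10 instead of 1.15.

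**The case against.** The strongest reply is that there is no contradiction. The scale is absent from the secondary objectives, from the secondary outcomes named in Outcomes, from the measures described under Data collection and from Economic evaluation. Table 1 lists questionnaire content, including date of birth and medication, so a row in it is not automatically a modelled endpoint. If the general rule in Statistical methods means the named secondary outcomes, each patient-reported one has its baseline value. Nor does the scale's absence from the descriptive list show that it must be modelled, since that list also omits the comparison with 12 weeks ago and the problems with glove wear.

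This stands in large part. A reader might infer that a declared outcome cannot be analysed as planned; the document does not support that, because it never declares the scale an outcome or assigns it an analysis. A reader might also infer that only a crude, unadjusted or biased comparison remains. That does not follow either: randomisation keeps the 12-week comparison unbiased, and adjustment for the stratification variable and for baseline EQ-5D-3L or HAQ is still possible. Chance imbalance at baseline is already reflected in the standard error, so it is not a second harm on top of lost precision. Within-arm change is not an analysis that the protocol proposes for this scale.

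One part does not stand. The matter cannot simply be left to the analysis plan, because the gap lies in data collection. On the narrow reading, the protocol asks participants for a scored rating and gives it neither a baseline value nor a stated use.

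**Conclusion.** The point holds as a minor inconsistency in the schedule. Table 1 collects the 0-100 health-state scale once, while the comparable scored measures are collected twice, and the general analysis rule, if it reaches this scale, calls for a baseline value that is not collected. The consequence is a less precise comparison on this one scale: a standard error larger by at most a factor of about 1.09 to 1.40 than with own-baseline adjustment. That range rests on assumed correlations of 0.4 to 0.7 and a linear relation between baseline and follow-up; only the direction of the loss is certain. The conclusions on hand pain, the named patient-reported secondary outcomes and cost per QALY do not depend on it.

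**What to change.** In Table 1, tick 0 weeks in the Health Status row. Add the 0-100 scale to the baseline questionnaire beside the EQ-5D-3L items, and analyse it with the linear regression in Statistical methods, adjusting for the stratification variable and its own baseline value. If the baseline booklet already contains the scale, only the tick needs correcting.

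The cost is one extra item in a booklet that every participant completes before randomisation, and a booklet version change. Participants recruited before the change will have no baseline value. Because the booklet comes before randomisation, whether the value is missing cannot depend on the allocated arm; these participants can stay in the model with a simple imputed baseline, though the precision gain will be smaller.
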